### Objectives

This primary objective of this study is to develop, implement, and evaluate a multi-level intervention comprising individual-, interpersonal-, and community-level components to reduce loneliness and enhance well-being among older adults in Hong Kong. The specific goals are to:

Evaluate the short-term effectiveness of the individual-level intervention, compared with an education-only control group in reducing loneliness.Assess the incremental benefit of adding an interpersonal-level intervention to the individual-level intervention in further reducing loneliness, compared with the individual-level intervention alone.Assess the incremental benefit of adding a community-level intervention to the combined individual- and interpersonal-level intervention in reducing loneliness.Examine potential mediators through which individual-, interpersonal-, and community-level interventions influence loneliness outcomes.Examine the long-term effects of the individual-level only, individual- + interpersonal-level; and individual- + interpersonal- + community-level interventions, compared with an education-only control group, on loneliness, physical and mental health, cognitive functioning, and healthcare utilization.Evaluate the cost-effectiveness of individual-level only, individual- + interpersonal-level; and individual- + interpersonal- + community-level interventions compared with education-only control group.

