### Sampling and two-stage cluster randomization

Our study will employ a cluster randomized controlled trial (cRCT) design, with public housing estates as the units of randomization. A cRCT was selected because the community-level intervention is delivered at the cluster-level and is likely to influence social interactions among residents within the same estate, making individual randomization impractical and increasing the risk of contamination. All individuals within each cluster will receive the same intervention, outcomes will be measured at the individual level, and analyses will account for clustering effects (49).

A two-stage cluster-random sampling approach will be used. In the first stage, 32 clusters will be randomly selected from the 260 public rental housing estates across Hong Kong and assigned to one of the four intervention arms by an independent researcher using 
*Random.org*
. The number of clusters may be adjusted if recruitment feasibility or cluster sizes vary. To minimize contamination, public rental housing estates assigned to different study arms will be geographically separated by at least 5 km, with a reasonable walking time of approximately 30 min or more. Figure 3 illustrates several estates located at least 5 km away from Oi Man estate, situated in the Kowloon City District. These estates include Tsz Hong Estate and Choi Wan II Estate in Wong Tai Sin District, as well as Wan Hon Estate in Kwun Tong District, with a walking time of at least 85 min. This spatial separation strategy is designed to reduce interaction between participants from different intervention arms, thereby maintaining the integrity of our intervention effects. In the second-stage, public rental housing units within each selected estate will be randomly sampled, and eligible residents will be invited to participate. This two-stage approach ensures an unbiased representation of older adults within each estates, while accounting for variation in cluster size.

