For the focus group discussions, all recordings will be transcribed verbatim by a research assistant. Two independent researchers will then conduct a thematic analysis of the transcripts using NVivo version 15 (95). The research team will review and agree on the identified codes, organizing them into main categories and subcategories. These categories may be condensed and reorganized as needed. The team will ensure consistency, reach consensus on the meaning and structure of the categories, and develop a finalized list. Ultimately, a set of categorized themes with supporting verbatim quotes will be produced to highlight the major strengths and limitations of the interventions and to inform improvements for their future implementation.

To evaluate the cost-effectiveness of the multi-level intervention compared to the control group, a trial-based economic evaluation will be conducted. Health outcomes will be measured as quality-adjusted life years (QALYs), calculated using the standard area-under-the-curve method based on individual EQ-5D-5L responses over the study period. Resource utilization will be estimated from the provider’s perspective, and costs for the intervention, outpatient care, emergency department visits, and inpatient care will be calculated using a bottom-up costing approach. The multi-level intervention will be considered dominant if it achieves higher QALYs at a lower cost than the control group. If it results in higher QALYs but also higher costs, the incremental cost-effectiveness ratio (ICER), defined as the difference in cost divided by the difference in QALYs (ΔCost/ΔQALYs), will be calculated. The intervention will be deemed cost-effective if it is dominant or if the ICER falls below the accepted willingness-to-pay threshold. The probability of the intervention to be accepted as cost-effective will be evaluated by probabilistic sensitivity analysis over the uncertainties of all parameters of costs and QALYs as well as variation of willingness-to-pay threshold from zero to 3× gross domestic product per capita in Hong Kong, presented as acceptability curves.

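### The economic analysis states no adjustment of incremental QALYs for baseline EQ-5D-5L utility, so the ICER and acceptability curves would be less precise than the collected data allow

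*Protocol article*

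**What the plan says.** All of this is in the economic paragraph of Planned statistical analysis, except where noted.

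- QALYs are "calculated using the standard area-under-the-curve method based on individual EQ-5D-5L responses over the study period". The ICER is then the cost difference divided by the QALY difference. Adjustment for baseline utility is neither stated nor excluded.
- Dominance: "The multi-level intervention will be considered dominant if it achieves higher QALYs at a lower cost than the control group".
- Verdict: "The intervention will be deemed cost-effective if it is dominant or if the ICER falls below the accepted willingness-to-pay threshold".
- Uncertainty: "The probability of the intervention to be accepted as cost-effective will be evaluated by probabilistic sensitivity analysis over the uncertainties of all parameters", shown as acceptability curves with "variation of willingness-to-pay threshold from zero to 3× gross domestic product per capita in Hong Kong". The text does not say how that probability bears on the verdict.
- Objectives calls for three comparisons: "Evaluate the cost-effectiveness of individual-level only, individual- + interpersonal-level; and individual- + interpersonal- + community-level interventions compared with education-only control group".
- Table 1 schedules the quality-of-life measure at T0 and at every later visit.
- Sampling and two-stage cluster randomization: "32 clusters will be randomly selected from the 260 public rental housing estates across Hong Kong", to be divided among four arms.

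**The concern.** An area-under-the-curve QALY includes the T0 utility, which treatment cannot have changed. Because utility persists within a person, a chance T0 difference between arms also reappears at each later visit. With about 8 estates per arm such differences are to be expected. In a raw comparison of mean QALYs they count as QALY gained or lost.

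The clinical outcomes are treated differently. Their mixed model has T0 as a time point and a group-by-time interaction, so the contrasts are changes from T0. The QALY difference as stated has no such step.

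What is at stake is precision. The incremental QALY is the denominator of the ICER and one of the two inputs to the acceptability curve, so avoidable noise in it widens both. It also feeds a verdict sentence that has no term for uncertainty.

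**Working it through.** The article gives no figure for the precision of the economic comparison, so there is none to reproduce.

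**Inputs from the article.** Visits at 0, 2, 4 and 6 months, then 12 and 24 months after the intervention ends, i.e. 18 and 30 months from baseline (Measures). 32 estates, so 8 per arm if split equally. 336 participants per arm, so 42 per estate; 15% attrition leaves about 36 per estate, or 288 per arm. ICC 0.028, stated for the loneliness scale only.

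**Assumptions, not in the article.** Utility SD 0.20 at each visit; equal within-person correlation ρ between all visits, 0.5 to 0.7; the same ICC of 0.028 for utility and QALYs; the same T0-to-QALY relation between estates as within them.

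**Step 1: QALY weights.** The trapezoid rule gives 0.083, 0.167, 0.167, 0.583, 1.0 and 0.5 years. They sum to 2.5, and their squares sum to 1.653.

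**Step 2: share of QALY variance explained by T0 utility.** In units of the utility variance:
- QALY variance: V = 2.5²ρ + 1.653(1 − ρ)
- Slope of QALY on T0 utility: b = 2.5ρ + 0.083(1 − ρ)
- R² = b²/V, and the variance inflation from omitting T0 is 1/(1 − R²)

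| ρ | V | b | R² | 1/(1 − R²) |
|---|---|---|---|---|
| 0.5 | 3.95 | 1.29 | 0.42 | 1.7 |
| 0.6 | 4.41 | 1.53 | 0.53 | 2.1 |
| 0.7 | 4.87 | 1.78 | 0.65 | 2.8 |

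Outside the assumed range, at ρ = 0.3, V = 3.03 and b = 0.81, so R² = 0.22. The gain is then smaller. It would also shrink if correlation fades with time, since most of the weight lies at 18 and 30 months.

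**Step 3: standard error of the incremental QALY at ρ = 0.6.** QALY SD = 0.20 × √4.41 = 0.420. Design effect = 1 + 35 × 0.028 = 1.98. Unadjusted SE = 0.420 × √(2 × 1.98/288) = 0.049. Adjusted SE = 0.049 × √(1 − 0.53) = 0.034.

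**Step 4: what a chance baseline gap does.** The SE of the T0 difference between two arms is 0.20 × √(2 × 1.98/288) = 0.023. A gap of that size becomes an apparent QALY difference of 0.023 × 1.29 = 0.03 (ρ = 0.5) to 0.023 × 1.78 = 0.04 (ρ = 0.7). Only 0.083 × 0.023 = 0.002 of it enters through the T0 term itself; the rest is persistence.

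**Step 5: the verdict sentence.** For one arm it reduces to two conditions: incremental QALY above 0, and threshold × incremental QALY − incremental cost above 0. Suppose there is no effect on health or healthcare use. With k = delivery cost ÷ SE of net benefit, the chance of a positive net benefit is Φ(−k): 50%, 40%, 31% and 16% at k = 0, 0.25, 0.5 and 1. Requiring a positive incremental QALY as well can only lower these. About one half per arm is therefore the upper limit, approached when delivery is cheap relative to threshold × SE of the incremental QALY.

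**The case against.** **The article is silent on adjustment; it does not rule it out.** The area-under-the-curve wording defines each person's QALY, not how arms are compared. An article may leave the regression to the full analysis plan, and randomisation keeps the raw difference unbiased on average. All of that stands. It limits the point to an improvement in precision and rules out a charge of bias.

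**Uncertainty is already covered by the acceptability curves.** Deciding on expected net benefit, with such curves alongside, is a recognised approach. This stands too, so the second part is a suggestion about reporting only.

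Three stronger readings are tempting and are not supported.

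- *A trial in which nothing works would usually endorse some arm.* With no effect on health or healthcare use, simulation over assumed inputs put the chance that at least one of three arms passes anywhere from 4% to 75%. Utility SD, costs, threshold and the ICC for utility are not in the article, and it sets no any-arm criterion. Lack of baseline adjustment would not be the main driver: adjusting lowered that chance by about 4 percentage points on average.
- *The rule cannot tell a useless programme from a useful one.* It can. Take SE 0.049, cost SD 6,000, QALY-cost correlation −0.3, delivery cost 500 and threshold 50,000 (all assumed, one currency). An arm then passes about 42% of the time with no effect, 76% with a true gain of 0.05 QALY and 95% with 0.10.
- *A 0.95 probability should be required.* With the same inputs and no baseline adjustment, that bar would pass a true gain of 0.05 QALY in only 18% of trials and 0.10 in 50%. This is a policy trade-off, and the article is not wrong to leave it out.

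A reader might also take the verdict to rest only on the direction of the estimates. The ICER is compared with a threshold, so magnitude counts.

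**Conclusion.** The point holds as a free improvement, not as an error that biases the result. As stated, the incremental QALY would carry chance T0 imbalance from about 8 estates per arm. Under assumed within-person correlations of 0.5 to 0.7, ignoring T0 utility leaves 42 to 65% of QALY variance unexplained that could be explained. A baseline gap of one standard error (0.023 at an assumed utility SD of 0.20) would appear as 0.03 to 0.04 QALY. The R² values do not depend on the utility SD. They do depend on the correlation and on its holding out to 30 months.

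The secondary point rests on the wording itself: the verdict uses point estimates, and the planned probability does not enter it. Up to about one half per arm is the limiting case for an arm with no health effect and cheap delivery, and should not be read as an expected error rate for this trial.

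**What to change.** In the economic paragraph of Planned statistical analysis, state that the incremental QALY for each active arm versus control is estimated by regressing individual QALYs on arm and T0 EQ-5D-5L utility, with estate accounted for. State also that this estimate is the one used in the ICER, net benefit and acceptability curves. If the full analysis plan already says so, a clause in the article is enough.

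As a reporting suggestion, add that wherever an arm is described as cost-effective, its incremental net benefit with a 95% CI and its planned probability of cost-effectiveness appear beside the verdict, for each of the three arms. No probability cut-off is needed.

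The cost is one covariate and two or three sentences. T0 utility is already scheduled for collection, so no visits, participants or data are added, and readers who decide on expected value keep the ICER.

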### Sample size estimation

Based on a previous cluster randomized controlled trial designed to detect a difference between control and intervention groups for a continuous outcome (i.e., UCLA Loneliness Scale), an estimated variance was calculated at a two-tailed 5% level of significance, power of 95%, targeting a 0.087 unit difference on the UCLA Loneliness Scale while maintaining a relative precision of ±3.0% (49–52). Taking into account a 15% attrition rate across 24 months (53), unequal cluster sizes, intervention non-adherence, and potential ICC variability of *ρ* = 0.028, an effective sample size of 1,344 participants will be required, with 336 participants in each arm.

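### The plan's definition of cost-effective cannot accept a result with fewer QALYs and lower cost, so acceptability curves built on it are biased downward, most at a threshold of zero

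*Protocol article*

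**What the plan says.** The protocol article, Planned statistical analysis, sets out a trial-based economic evaluation in four linked statements.

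- Dominance: "The multi-level intervention will be considered dominant if it achieves higher QALYs at a lower cost than the control group".
- The ratio is introduced under a condition: "If it results in higher QALYs but also higher costs, the incremental cost-effectiveness ratio (ICER" is then defined as the cost difference over the QALY difference.
- The decision rule: "The intervention will be deemed cost-effective if it is dominant or if the ICER falls below the accepted willingness-to-pay threshold".
- Uncertainty: "The probability of the intervention to be accepted as cost-effective will be evaluated by probabilistic sensitivity analysis over the uncertainties of all parameters". The parameters meant are those for QALYs and costs, and the same sentence sets the threshold range: "variation of willingness-to-pay threshold from zero to 3× gross domestic product per capita in Hong Kong, presented as acceptability curves".

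The article gives no rule for a result with fewer QALYs and does not mention net benefit. It does not say how a single simulated draw is classed. It gives no expected costs, QALYs, standard errors or correlation.

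**The concern.** The decision rule covers only half of the cost-effectiveness plane, the half where QALYs rise. Simulated draws of the cost and QALY differences will generally fall on both sides of zero QALY difference. The uncertainty sentence refers to acceptance as cost-effective directly after that term has been defined, and offers no other criterion. The natural reading is therefore that the same rule is counted over the draws.

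On that reading, a draw with fewer QALYs and lower cost can never be accepted. Some of these draws should be, namely those where the saving is worth more at the given threshold than the QALYs lost. The acceptability curves are the only expression of uncertainty stated for the cost-effectiveness goal, which the Introduction says is to inform resource allocation. The planned threshold range also includes zero, the point where the error is largest.

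**Working it through.** **Inputs.** From Planned statistical analysis: the dominance rule, the condition for calculating the ICER, the decision rule, and a threshold λ running upward from zero. The protocol states no figure that could be reproduced. The rest is assumed: the QALY difference dQ and cost difference dC are bivariate normal, each in units of its own SE, with correlation ρ, and λ is in units of SE(cost)/SE(QALY).

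**Step 1: compare the rules by quadrant.** The reference is positive net monetary benefit, λ·dQ − dC > 0.

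- More QALYs, lower cost: both rules accept.
- More QALYs, higher cost: both accept when dC/dQ < λ.
- Fewer QALYs, higher cost: both reject.
- Fewer QALYs, lower cost: the written rule always rejects; net benefit accepts when dC < λ·dQ.

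The two rules differ only in the last quadrant.

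**Step 2: the shortfall.** Shortfall(λ) = P(dQ < 0 and dC < λ·dQ). As λ rises, λ·dQ becomes more negative for every dQ < 0. The region therefore shrinks, whatever the distribution. At λ = 0 the shortfall is P(dQ < 0 and dC < 0): the correct curve equals P(cost saving), while the written rule gives P(dominance).

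**Step 3: size at λ = 0.** With both means zero, P(dQ < 0 and dC < 0) = 1/4 + arcsin(ρ)/(2π). For ρ = ±0.5 this is 1/4 ± 1/12. With ρ = 0 it is the product of the two tail areas. For any ρ it cannot exceed the smaller of P(dC < 0) and P(dQ < 0).

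| Mean dC (SE) | Mean dQ (SE) | ρ | Net benefit | Written rule | Shortfall (points) |
|---|---|---|---|---|---|
| 0 | 0 | 0 | 50% | 25% | 25 |
| 0 | 0 | +0.5 | 50% | 17% | 33 |
| 0 | 0 | −0.5 | 50% | 33% | 17 |
| +1 | 0 | 0 | 16% | 8% | 8 (0.159 × 0.5) |
| +2 | 0 | any | 2.3% | – | at most 2.3 |
| any | +1.96 | any | – | – | at most 2.5 |
| −1 | 0 | 0 | 84% | 42% | 42 (0.841 × 0.5) |

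By simulation, letting ρ run from −0.5 to +0.5 gives 3 to 13 points in the +1 SE cost row and 37 to 47 points in the −1 SE cost row.

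**Step 4: decline with λ.** With both means zero and ρ = 0, the misclassed region is a wedge of angle 90° − arctan(λ), so the shortfall is that angle divided by 360°.

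- λ = 0: 90/360 = 25 points.
- λ = 1: 45/360 = 12.5 points (50% against about 38%).
- λ = 2: 26.6/360 = 7.4 points.
- λ = 5: 11.3/360 = 3.1 points.

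**The case against.** The strongest reply is that the article never says how a draw is classed. Acceptability curves are a named method, conventionally computed as the probability of positive net benefit, and a fuller analysis plan may say so. This stands in part: that draws will be misclassed is an inference. However, the published text does define the term it then attaches a probability to, and that definition is wrong for this use, not merely brief.

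A second reply is that large errors need special conditions. That is correct. The active arms receive 8 or 16 weekly 60-minute telephone sessions plus maintenance or community sessions, while the control arm receives monthly messages, so a clear cost increase is plausible and the error would then be small. Against this, delivery is by volunteers reimbursed in vouchers, and outpatient, emergency and inpatient costs are counted and could offset delivery cost. The sample size is set on the UCLA Loneliness Scale and not on QALYs, so an uncertain QALY difference is realistic. Neither case can be ruled out beforehand.

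A reader might infer three stronger points, which the document does not support.

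- That a negative ratio from a costlier draw with fewer QALYs would count as below the threshold. The article limits the ICER to higher QALYs with higher costs, so this contradicts its text.
- That all draws with fewer QALYs are misclassed. Costlier ones are correctly rejected, as are cheaper ones whose saving does not cover the QALY loss.
- That the draws ignore clustering or separate each participant's cost from the same participant's QALYs. The section says that all analyses account for the cluster design, and nothing in it says that costs and QALYs are drawn unpaired.

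**Conclusion.** The point holds in conditional form. The only stated definition of cost-effective cannot accept fewer QALYs at lower cost. If the acceptability curves use it, they are biased downward and never upward, and at a threshold of zero they show the probability of dominance in place of the probability of saving money.

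The direction, the value at zero and the decline with the threshold are exact and need no distributional assumption. The numerical sizes rest on bivariate normality and on assumed means and correlation. They run from negligible, when costs clearly rise or the QALY gain is clear, to 25 points or more at a low threshold, when costs are about equal or lower and there is little or no QALY gain. No unconditional size can be claimed from the protocol.

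**What to change.** Replace the decision rule with one criterion for both the point estimate and each draw: accept when threshold × difference in QALYs − difference in cost is greater than zero. Define the acceptability curve as the probability of positive net monetary benefit, plotted from zero to three times GDP per capita as already planned. Dominance and the ICER can still be reported as descriptions.

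The new criterion agrees with the present rule wherever QALYs rise, so no conclusion in that half of the plane changes. The cost is a sentence or two of protocol text and a line of code, with no new data.

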### Ethical considerations and dissemination

The trial has been approved by the Human Research Ethics Board of The Education University of Hong Kong (2023-2024-0624) and is prospectively registered with ClinicalTrials.gov (NCT07123064). Prior to enrolment, all participants will receive detailed written information about the study and provide written informed consent. Signed informed consent will be obtained before any study procedures commence. Recruitment will adhere to the principle of voluntariness, and all participants’ data will be kept confidential. Participants will receive supermarket vouchers upon completion of the intervention and assessments. If a participant decides to withdraw from the study, their wishes will be complied with, and reasons for the withdrawal will be sought. Findings from this trial will be widely disseminated through press conferences, scientific conferences, peer-reviewed journals, and stakeholder organizations.

